#### Control group

Standardized medical therapy of T2DM and its co-morbidities are defined as the use of the latest S3 Guidelines by the German Diabetes Association [8,9].

#### Study visits

From screening to last control 8 years after randomization there will be 12 study visits assessing laboratory parameters for diabetes, regular laboratory parameters, blood pressure, resting 12-lead electrocardiogram amount of medication, morbidity and mortality, especially nephropathy, retinopathy, peripheral neuropathy, and quality of life (Figure 2).

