**Methods:**

The DiaSurg 2 trial is a multicenter, open randomized controlled trial comparing RYGB including standardized medical treatment if needed to exclusive standardized medical treatment of T2DM (control group). The primary endpoint is a composite time-to-event endpoint (cardiovascular death, myocardial infarction, coronary bypass, percutaneous coronary intervention, non-fatal stroke, amputation, surgery for peripheral atherosclerotic artery disease), with a follow-up period of 8 years. Insulin-dependent T2DM patients aged between 30 and 65 years will be included and randomly assigned to one of the two groups. The experimental group will receive RYGB and, if needed, standardized medical care, whereas the control group will receive exclusive standardized medical care, both according to the national treatment guidelines for T2DM. Statistical analysis is based on Cox proportional hazards regression for the intention-to-treat population. Assuming a loss to follow-up rate of 20%, 200 patients will be randomly allocated to the comparison groups. A total sample size of *n* = 400 is sufficient to ensure 80% power in a two-tailed significance test at alpha = 5%.

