#### Primary endpoint

The primary endpoint is the time from randomization to one of the composite events, including death from cardiovascular causes, non-fatal myocardial infarction, coronary artery bypass grafting, percutaneous coronary intervention, non-fatal stroke, amputation, and surgery for peripheral atherosclerotic artery disease during the follow-up of at least 8 years according to the Steno 2 study. End-organ damage is also specified according to the Steno2 study from Gaede *et al.*[31,32]. Together with the expected accrual period of 2 years, this amounts to a maximum follow-up period of 10 years. If none of the above events are observed within the follow-up period, the date of the last follow-up is censored.

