#### Secondary endpoints

Secondary endpoints include the time to death from any cause and the time to each component of the primary endpoint. In addition, laboratory parameters for T2DM (HbA1c, C-peptide and glucagon stimulated C-peptide, fasting glucose, fasting insulin, oral glucose tolerance test), regular laboratory parameters (that is, lipid profiles, serum creatinine, creatinine clearance) as well as vitamins and micronutrients (vitamin B6, B12, folate acid, and iron status) are assessed. Additional parameters include the amount of medication (insulin dosage, metformin, antihypertensive therapy, and so on), the assessment of nephropathy (urine albumin excretion 24-h urine sample), retinopathy (according to the EURODIAB six-level grading scale), peripheral neuropathy (assessed by biothesiometry of the big toe in both feet and questionnaire), healthcare cost and quality of life. Parameters are assessed at 0, 3, 6, 12 months, and then yearly after surgery (Figure 2).

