### Statistical methods

#### Sample size

The study, with seven components as used in the Steno 2 study [31,32], is designed to demonstrate the superiority of the experimental group to the control group with respect to the hazard ratio for a composite event. The Steno2 study was used to estimate the rate of cardiovascular events we have to expect after 8 years of medical therapy. A reduction of diabetes-associated morbidity from 20%, as reported in the Steno 2 study for intensified conservative T2DM treatment, to 10% for surgical treatment will be defined as success and used for sample size calculation. Let *p*_S_ and *p*_C_ denote the cumulative incidence of one or more components of the composite endpoint for RYGB and standardized medical treatment, respectively. For exponentially distributed event times, event rates of *p*_S_ = 0.10 and *p*_C_ = 0.20 after 8 years correspond to a hazard ratio of 0.472 in favor of surgical treatment [31]. At the two-sided significance level of *α* = 5%, a total number of 56 events is required to detect this effect with a power of 80%. Assuming again exponentially distributed event times, an accrual period of 2 years and a minimal follow-up time of 8 years, the required number of patients to achieve this number of events is given by 336 in total, that is, 168 patients per treatment arm. Assuming a loss to follow-up rate of 20%, 200 patients should be randomly assigned to each intervention group (400 in total). This ensures sufficient power for the intention to treat analysis (ITT) and the complete cases per protocol (PP) analysis.

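### The sample size counts 8 to 10 years of follow-up per patient, but the visit schedule and the abstract stop at 8 years; the censoring rule must be reconciled

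*Protocol article*

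**What the plan says.** The protocol article describes follow-up for the primary endpoint in two ways.

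**8 to 10 years.** The sample-size calculation under Statistical methods assumes "an accrual period of 2 years and a minimal follow-up time of 8 years". The Primary endpoint section requires at least 8 years, adds the 2-year accrual and concludes that "this amounts to a maximum follow-up period of 10 years". Patients without an event are censored at their last follow-up.

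**8 years.** Under Study visits: "From screening to last control 8 years after randomization there will be 12 study visits". The abstract describes the composite time-to-event endpoint "with a follow-up period of 8 years", and the Discussion also speaks of 8 years.

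Three other places bear on the point:
- Recruitment and timelines gives 12 months of recruitment, but 120 months from first patient in to last patient out.
- The safety section has serious adverse events reported in both arms until the regular end of the trial or premature withdrawal.
- Secondary endpoints sets a different time origin for its assessments: "Parameters are assessed at 0, 3, 6, 12 months, and then yearly after surgery".

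**The concern.** Because event-free patients are censored at last follow-up, the date of last contact decides whether the years between 8 and 10 count. The sample size uses those years. The visit schedule, read as written, does not provide them. Two analysts could apply different censoring rules to the same data and each cite the protocol.

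Two things are at stake. First, if everyone is censored at 8 years, the stated patient number no longer yields the stated number of events. Second, if events after year 8 are counted, the article describes no scheduled contact for finding them. They would come in through serious adverse event reporting in an open trial. Such reporting could be less complete than visits and could differ between arms, but the documents give no figure for this.

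**Working it through.** **Inputs** (Statistical methods, Sample size): 20% (control) and 10% (surgery) with an event at 8 years, exponential event times, two-sided 5% level, 80% power, 2 years of accrual, at least 8 years of follow-up, 20% loss, 400 randomized. Allocation is 1:1 (Randomization). I assume uniform accrual.

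**1. Hazard ratio.** λ_C = −ln(0.8)/8 = 0.02789 and λ_S = −ln(0.9)/8 = 0.01317 per year. The ratio is 0.4722, as stated ("after 8 years correspond to a hazard ratio of 0.472 in favor of surgical treatment").

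**2. Required events (Schoenfeld).** D = 4(1.960 + 0.842)² / (ln 0.4722)² = 55.75, so 56. This reproduces the stated figure: "a total number of 56 events is required to detect this effect with a power of 80" per cent.

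**3. Patients, with 8 to 10 years each.** With accrual A = 2 and minimum follow-up F = 8, the event probability is 1 − [exp(−λF) − exp(−λ(A+F))]/(λA).
- Control: 0.2219
- Surgery: 0.1117
- Mean: 0.1668

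56/0.1668 = 335.7, so 336. The stated figure is reproduced, with 56.05 expected events and 80.2% power.

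**4. Same patients, all censored at 8 years.** The mean event probability is (0.20 + 0.10)/2 = 0.15.
- 336 × 0.15 = 50.4 events.
- Power = Φ(|ln 0.4722| × √50.4 / 2 − 1.960) = 75.9%.
- 56/0.15 = 373.3, so 374 evaluable patients would be needed for 56 events.

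**5. All 400 randomized, with loss treated as censoring.** The article does not say how loss is spread over time, so I assume an exponential loss hazard δ, equal in both arms. The event probability is λ/(λ+δ) × [1 − exp(−(λ+δ)T)].

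| Follow-up | Loss reaches 20% at | Expected events | Power |
|---|---|---|---|
| Fixed 8 years | 8 years | 54.0 | 78.7% |
| Fixed 8 years | 10 years | 55.1 | 79.5% |
| Fixed 8 years | no loss | 60.0 | 82.8% |
| 8 to 10 years, common close | 8 years | 59.2 | 82.3% |
| 8 to 10 years, common close | 10 years | 60.6 | 83.2% |

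**6. Recruitment period.** 24 + 96 = 120 months agrees with the 2-year accrual. 12 + 96 = 108 months does not reach the stated 120. With 12 months of recruitment and 336 evaluable patients:
- closing at the last patient's 8-year visit (8 to 9 years each) gives 53.2 events and 78.2% power;
- following everyone to month 120 (9 to 10 years each) gives 58.9 events and 82.1% power.

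**7. Visit count.** Screening, months 0, 3, 6 and 12, and years 2 to 8 make 1 + 4 + 7 = 12. This fits a schedule that ends at year 8, but is supporting evidence only.

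**The case against.** The strongest reply is that the endpoint definition governs. It states at least 8 and at most 10 years, the sample size uses the same window, and the 120 months equal 2 + 8 years. On that reading the Study visits section lists assessment visits and sets no censoring rule, and no events are lost. This stands in part. A reader might infer that the 56 events will not be reached. The documents do not support that, because the shortfall arises only if the visit schedule overrides the endpoint section.

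A reader might also infer that nothing is collected after year 8. That goes too far. Serious adverse event reporting runs in both arms to the regular end of the trial, and nearly all components of the primary endpoint would qualify as deaths, hospitalizations or life-threatening events. What remains is that this is reporting, not scheduled contact.

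The count of 12 visits does not prove that later contacts are absent. It is given for the period up to year 8, the study-flow figure is not shown, and the Discussion adds a 1-month visit for surgical patients. The full protocol may hold more than the article.

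A lower power of 73.9% (48.0 events from 320 patients) could be quoted, taking 400 less 20% who contribute nothing. It mixes in a separate matter: 336/0.8 is 420, not 400. Even with 8 to 10 years of follow-up, 320 patients give only 53.4 events and 78.3% power. That figure should not be charged to the follow-up rule.

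The reply does not remove the conflict itself. The article fixes a last visit at year 8, repeats 8 years in the abstract, and sizes the trial on longer observation.

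**Conclusion.** The contradiction is real and touches both a stated figure and the censoring of the primary endpoint. It should be fixed, but it is an inconsistency to reconcile and not a flawed design choice.

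If all patients are censored at 8 years, the protocol's own 336 evaluable patients give 50.4 events and 75.9% power in place of 56 and 80%. With 400 randomized and gradual 20% loss, the figures are 54.0 to 55.1 events and 78.7% to 79.5% power, within about 1.3 percentage points of the target. With a common closing date after a 2-year accrual there is no shortfall. These results rest on the protocol's event rates, exponential times, uniform accrual and, for the 400, the assumed loss pattern.

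The assessment clock that starts at surgery is a separate, minor matter. Controls have no surgery date, and surgery may follow allocation by up to 2 months. It concerns secondary parameters that are analysed descriptively; the primary endpoint runs from randomization.

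**What to change.** Reconcile the abstract, Recruitment and timelines, Study visits, Primary endpoint and the sample-size text, in one of two ways.

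- **Common closing date.** Define it as the last randomized patient's 8-year visit. Provide annual contacts for primary events in both arms until then, and censor event-free patients at that date, or earlier if they are lost. State one recruitment period: the 2-year accrual puts closure at month 120, whereas 12 months of recruitment puts it at month 108 and changes the expected events as shown in step 6.
- **Fixed 8 years.** Remove the 10-year maximum, state censoring at 8 years, and restate the calculation: 50.4 events and 76% power for 336 evaluable patients, or about 54 to 55 events and 79% power for 400 with loss as censoring. Keeping 56 events would need 374 evaluable patients. The recruitment period and the 120 months still have to be aligned.

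Separately, anchor the secondary-parameter visits at randomization in both arms.

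The first option costs at most about two further annual contacts for patients enrolled early, within the 120 months already planned. The second costs only wording and a slightly lower stated power.

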**Figure 2 F2:**
[figure not shown]
Study flow for the duration of the entire trial.

### Risk-benefit ratio

RYGB is an established method in bariatric surgery, with low mortality rates of 0.16% to 0.5% in experienced hands [20,28]. Morbidity rates for all-cause complications range between 2% and 10% [20]. Long-term risk for secondary disease due to malabsorption (deficiency in vitamins, foliate, or iron balance) are known and are managed by administering life-long vitamin supplementation [29]. Another possible side effect of RYGB is the dumping syndrome. The risk of surgery for non-severely obese diabetic patients is difficult to assess because there are hardly any data. Due to the fact that patients are not as obese as in bariatric surgery, both reduced morbidity and reduced mortality rates are expected. In recent studies involving non-severely obese patients suffering T2DM, the postoperative mortality rate was found to be 0%, and only 1.2% if the operated patients needed revision due to postoperative complications [19,25,27,30].

### Outcome

The chosen primary and secondary endpoints cover outcomes from different perspectives (for example, patient, surgeon, healthcare system), allowing for a comprehensive evaluation of the surgical treatment of T2DM, especially as to whether long-term T2DM-associated morbidity and mortality can be diminished and which other factors, apart from glycemic control, are dominant.

#### Primary endpoint

The primary endpoint is the time from randomization to one of the composite events, including death from cardiovascular causes, non-fatal myocardial infarction, coronary artery bypass grafting, percutaneous coronary intervention, non-fatal stroke, amputation, and surgery for peripheral atherosclerotic artery disease during the follow-up of at least 8 years according to the Steno 2 study. End-organ damage is also specified according to the Steno2 study from Gaede *et al.*[31,32]. Together with the expected accrual period of 2 years, this amounts to a maximum follow-up period of 10 years. If none of the above events are observed within the follow-up period, the date of the last follow-up is censored.

#### Secondary endpoints

Secondary endpoints include the time to death from any cause and the time to each component of the primary endpoint. In addition, laboratory parameters for T2DM (HbA1c, C-peptide and glucagon stimulated C-peptide, fasting glucose, fasting insulin, oral glucose tolerance test), regular laboratory parameters (that is, lipid profiles, serum creatinine, creatinine clearance) as well as vitamins and micronutrients (vitamin B6, B12, folate acid, and iron status) are assessed. Additional parameters include the amount of medication (insulin dosage, metformin, antihypertensive therapy, and so on), the assessment of nephropathy (urine albumin excretion 24-h urine sample), retinopathy (according to the EURODIAB six-level grading scale), peripheral neuropathy (assessed by biothesiometry of the big toe in both feet and questionnaire), healthcare cost and quality of life. Parameters are assessed at 0, 3, 6, 12 months, and then yearly after surgery (Figure 2).

### Data management

All protocol-required information collected during the trial is entered in the case report form (CRF) by the investigator or a designated representative at the respective participating center. Investigators are expected to complete documentation as soon as possible after the information is collected, preferably on the same day that a trial participant is seen for an examination, treatment, or any other trial procedure.

The completed CRF must be reviewed and signed by the investigator named in the trial protocol or by a designated sub-investigator. After keeping a copy at the trial center, the original CRF is sent to the University of Heidelberg for data entry. Double data entry is carried out to ensure the correct transfer of data from the CRF to the database. Completeness, validity, and plausibility of data are examined by validating programs that thereby generate queries which need to be clarified by the investigator. At the end of the trial, the principle investigator will retain the original CRFs. All data are managed and analyzed by the Study Center of the German Surgical Society (SDGC) at the University of Heidelberg in cooperation with R&P GmbH (Burscheid, Germany) as contract research organization.

### Safety evaluation and reporting of adverse events

During and following a patient’s participation in the trial, the investigator ensures that adequate medical care is provided. The patient receives adequate treatment in any clinical situation, including emergencies, and outcome of the patient must be controlled. A serious adverse event is an event that results in death, is immediately life-threatening, requires or prolongs hospitalization, results in persistent or significant disability or incapacity, or requires re-operation. From the day the patient has signed informed consent until the regular end of the trial, or until premature withdrawal of the patient, all serious adverse events are documented and reported to the principal investigator within 24 h.

### Statistical methods

#### Sample size

The study, with seven components as used in the Steno 2 study [31,32], is designed to demonstrate the superiority of the experimental group to the control group with respect to the hazard ratio for a composite event. The Steno2 study was used to estimate the rate of cardiovascular events we have to expect after 8 years of medical therapy. A reduction of diabetes-associated morbidity from 20%, as reported in the Steno 2 study for intensified conservative T2DM treatment, to 10% for surgical treatment will be defined as success and used for sample size calculation. Let *p*_S_ and *p*_C_ denote the cumulative incidence of one or more components of the composite endpoint for RYGB and standardized medical treatment, respectively. For exponentially distributed event times, event rates of *p*_S_ = 0.10 and *p*_C_ = 0.20 after 8 years correspond to a hazard ratio of 0.472 in favor of surgical treatment [31]. At the two-sided significance level of *α* = 5%, a total number of 56 events is required to detect this effect with a power of 80%. Assuming again exponentially distributed event times, an accrual period of 2 years and a minimal follow-up time of 8 years, the required number of patients to achieve this number of events is given by 336 in total, that is, 168 patients per treatment arm. Assuming a loss to follow-up rate of 20%, 200 patients should be randomly assigned to each intervention group (400 in total). This ensures sufficient power for the intention to treat analysis (ITT) and the complete cases per protocol (PP) analysis.

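### Randomising 400 does not keep the plan's own 336 patients after a 20% loss, so the power assurance for the complete-case per-protocol analysis is not supported; the ITT analysis is not shown to be underpowered

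*Protocol article*

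**What the plan says.** The sample-size section under Statistical methods in the protocol article builds the number in steps. The target is "A reduction of diabetes-associated morbidity from 20%, as reported in the Steno 2 study for intensified conservative T2DM treatment, to 10% for surgical treatment", and with exponential event times these rates "correspond to a hazard ratio of 0.472 in favor of surgical treatment". Then "a total number of 56 events is required to detect this effect with a power of 80"%. With 2 years of accrual and at least 8 years of follow-up, "the required number of patients to achieve this number of events is given by 336 in total", or 168 per arm. The loss allowance follows: "Assuming a loss to follow-up rate of 20%, 200 patients should be randomly assigned to each intervention group (400 in total"). The section closes with an assurance for two analyses: "This ensures sufficient power for the intention to treat analysis (ITT) and the complete cases per protocol (PP) analysis". The abstract repeats the 20% loss and says that n = 400 "is sufficient to ensure 80% power in a two-tailed significance test".

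Three other sections bear on the point:

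- Primary endpoint: patients without an event are censored at their last follow-up.
- Analysis of the primary endpoint: the confirmatory test is a Cox regression on the ITT population, and patients with major protocol deviations leave the PP set.
- Secondary analyses: the PP analysis is a sensitivity analysis.

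**The concern.** The step from 336 to 400 does not match a 20% loss. Taking 20% away from 400 leaves 320, which is 16 fewer than the section has just said are needed. The article gives no formula for the step.

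This matters most for the sentence on the PP analysis. A complete-case set leaves out the lost patients by definition, so the 20% comes off in full, and major deviators come off after that. Readers who rely on that sentence would believe that the PP sensitivity analysis meets the same power standard as the main one. The total of 400 is also the trial's headline figure, repeated in the abstract, so the assumption that makes it adequate should be visible.

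**Working it through.** **Inputs** (all from the protocol article's sample-size section unless noted): two-sided alpha 5%; power 80%; 8-year event rates 0.20 (control) and 0.10 (surgery); exponential event times; accrual 2 years; minimum follow-up 8 years; loss 20%; 1:1 allocation (Randomization).

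**1. Reproducing the plan up to 336**

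- Hazards: control -ln(0.8)/8 = 0.02789; surgery -ln(0.9)/8 = 0.01317.
- Hazard ratio: ln(0.9)/ln(0.8) = 0.472, with |ln HR| = 0.7504.
- Events (Schoenfeld): 4(1.960 + 0.842)²/0.7504² = 55.75, so 56.
- Event probability with uniform accrual: 1 - (e^(-8λ) - e^(-10λ))/(2λ), which is 0.2219 (control) and 0.1117 (surgery), mean 0.1668.
- Patients: 56/0.1668 = 335.7, so 336.

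Every figure agrees with the plan.

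**2. The loss step**

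- Patients to randomise so that 336 remain: 336/(1 - 0.20) = 420, or 210 per arm.
- Patients left from 400: 400 × 0.80 = 320.
- Loss that 400 does cover: 1 - 336/400 = 16%.

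**3. Complete-case power with 400 randomised**

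Power = Φ(√E/2 × 0.7504 - 1.96), where E is the number of events.

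| Patients analysed | Events | Power |
|---|---|---|
| 336 (the plan's requirement) | 56.1 | 80.2% |
| 320 (20% loss only) | 53.4 | 78.3% |
| 304 (a further 5% excluded) | 50.7 | about 76% |
| 288 (a further 10% excluded) | 48.0 | about 74% |

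The 5% and 10% exclusions are my assumption; the article gives no rate of major deviations.

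**4. ITT power with 400 randomised**

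Here a lost patient counts until censored. The article does not say when loss occurs, so I assume an exponential loss hazard η that reaches 20% by year 8 (η = 0.0279) or by year 10 (η = 0.0223). With t = λ + η, the event probability is (λ/t) × [1 - (e^(-8t) - e^(-10t))/(2t)].

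| Timing of 20% loss | Mean event probability | Events from 400 | Power | Randomised for 56 events |
|---|---|---|---|---|
| By year 8 | 0.1481 | 59.2 | 82.3% | about 378 |
| By year 10 | 0.1516 | 60.6 | 83.2% | about 369 |

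**5. Sensitivity to the schedule**

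Recruitment and timelines plans 12 months of recruitment, against the 2 years used in the calculation. With 1-year accrual and an 8-year minimum, 320 complete cases give 50.7 events and 76.2% power. On the same schedule the ITT analysis of 400 gives 56.6 to 57.9 events and 80.6% to 81.5% power.

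**The case against.** The strongest reply is that power in a time-to-event analysis depends on events, not on completers. Lost patients in the confirmatory Cox model contribute until they are censored, so dividing by 0.8 treats them as giving nothing and overstates the need. This stands for the ITT analysis. A reader might infer from 336/0.8 = 420 that the trial misses its stated 80% power, or that the abstract's claim is false. The documents do not support that: the abstract ties its claim to the ITT Cox analysis, and step 4 shows more than 56 events from 400. ITT power would fall below 80% if every patient stopped at exactly 8 years (54.0 to 55.1 events, 78.7% to 79.5% power), but the primary-endpoint section sets at least 8 years and a maximum of 10.

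A second reply is that the section promises only sufficient power for the PP analysis, without naming 80%, and that this is a sensitivity analysis. That lowers the weight of the point. Yet 80% is the only power standard the section gives, and the assurance follows directly from it.

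A third reply is that the shortfall depends on the schedule. Recruitment and timelines also gives 120 months from first patient in to last patient out. If recruitment takes 12 months and everyone is followed to that common close, follow-up is 9 to 10 years, and 320 complete cases give 56.1 events and 80.2% power. This is correct, but it is not the schedule on which 336 was computed, and it leaves no room for PP exclusions.

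It is also tempting to say that the authors multiplied by 1.2 instead of dividing by 0.8, since 168 × 1.2 = 201.6. That would round up to 202, not 200. With no formula in the article, the cause cannot be established, and the point does not need it.

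**Conclusion.** The point holds in a limited form. As written, 400 randomised does not preserve the plan's 336 patients under a 20% loss. For the complete-case PP analysis, the calculation's own accrual and follow-up give 78.3% power at best, about 2 points and 2.6 events below what 336 patients would give. Any exclusion for protocol deviation lowers it further. The PP assurance is therefore unsupported at the plan's 80% standard.

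The confirmatory ITT analysis is not shown to be underpowered. That conclusion rests on loss being spread over follow-up and on lost patients being censored when lost. The article states the censoring rule but not the timing of loss. Only if all lost patients contributed no data at all would the ITT figure drop to the same 78.3%.

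Severity is minor to moderate: a correction to the stated figures, not a flaw in the primary test or a reason to enlarge the trial.

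**What to change.** Make three changes in the sample-size section, and carry the first two into the abstract:

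1. State what 400 covers. Either it allows for 16% of patients contributing no data, or, with 20% contributing no data, power is about 78% (53 events).
2. If 400 is kept alongside a 20% loss, say that lost patients contribute until censoring, and give the resulting ITT events and power with the assumed timing of loss (for example 59 to 61 events and 82% to 83% for exponential loss reaching 20% by year 8 to 10).
3. Delete the assurance for the complete-case PP analysis, or replace it with computed power that includes an explicit allowance for major deviations.

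When the figures are restated, use one accrual period, because Recruitment and timelines and the calculation differ.

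The cost is a few sentences and a slightly less favourable PP figure. No extra patients are needed. Only if the sponsor wants 80% complete-case power with a full 20% loss does the number become 420 (210 per arm), and that is before any PP exclusions.
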